## 5.8 Statistical software

The analysis will be carried out using SAS version 9.4. Other software such as R, Stata or python may be used if necessary.

## 5.9 Revisions to protocol

| Protocol                                                                                                                                                                                                                                                                                              | Changes in SAP                                                                                                                                                                                                                          | Justification                                                                                                                                                                                                                                                                                                                     |
|-------------------------------------------------------------------------------------------------------------------------------------------------------------------------------------------------------------------------------------------------------------------------------------------------------|-----------------------------------------------------------------------------------------------------------------------------------------------------------------------------------------------------------------------------------------|-----------------------------------------------------------------------------------------------------------------------------------------------------------------------------------------------------------------------------------------------------------------------------------------------------------------------------------|
| 
The primary outcome for the study was the change in SBP from baseline to 2-year follow-up.
 
The primary analysis of intervention effects will use a generalized estimating equation with an exchangeable covariance structure accounting for clustering and adjustment for baseline SBP.
 | 
The primary outcome for the study is changed to SBP evaluated during 24-month follow-up.
 
A pre-specified linear mixed effects model will be performed to model repeated measures of SBP of the same individual over time.
 | 
To account for the impact of missing data due to high mortality and leaving from the residential facilities, all available follow-up data in SBP will be used instead of that just in 24-month alone. Thus, linear mixed model, which naturally fits to hierarchical data, is more appropriate than GEE in such situation.
 |
| 
Continuous secondary outcomes were changes in diastolic blood pressure; serum potassium; and 24-hour urinary sodium, potassium, and microalbumin excretion.
                                                                                                                                    | 
Like the primary outcome SBP, all continuous secondary outcomes are change to the mean level evaluated during 24-month follow-up
                                                                                                 | 
Same as above.
                                                                                                                                                                                                                                                                                                             |
|                                                                                                                                                                                                                                                                                                       | 
Add secondary outcomes: Incidence of renal dysfunction: A new case of renal dysfunction is defined as having eGFR <60 at either 12 or 24 months, regardless of clinical manifestations.
                                       | 
We are particularly interested in the safety concerns about salt reduction strategies. Renal dysfunction is a potential side effect of salt reduction.
                                                                                                                                                                     |

## 6 Main tables and figures

### 6.1 Tables

**Table 1. Baseline Characteristics of study population**

|  | All
N = | SS+SSSC
N = | SSSC
N = | SS
N = | control
N = | p value |
|--|------------|----------------|-------------|-----------|----------------|---------|
|--|------------|----------------|-------------|-----------|----------------|---------|

#### Cluster level

Number of senior residential facilities, n

Number of study participants per facility, median (IQR)

#### Individual level

##### Demographics and anthropometrics

Age, mean(SD)

Male, n (%)

Number of participants by  
center, n (%)

Changzhi

Xi'an

Hohhot

Yangcheng

Education level, n (%)

Primary school and below

Secondary school

High school

Undergraduate & above

BMI, mean (SD)

**Life style**

Smoking status, n (%)

Current smokers

Ex-smoker

Never-smokers

Alcohol intake, n (%)

Yes

No

**Comorbidities**

Hypertension, n (%)

Yes

No

Coronary artery disease, n (%)

Yes

No

Diabetes, n (%)

Yes

No

Stroke, n (%)

Yes

No

Renal disease, n (%)

Yes

No

**Medication use**

Antihypertensive medication, n  
(%)

Yes

No

Potassium-sparing medications, n (%)

Yes

No

**Vital signs**

SBP, mean(SD)

DBP, mean(SD)

Pulse, mean(SD)

**Labs**

Total cholesterol, mean(SD)

LDL-C, mean(SD)

Triglycerides, median(IQR)

HDL-C, mean(SD)

Fasting glucose, mean(SD)

Serum potassium, mean(SD)

Serum sodium, mean(SD)

eGFR, mean(SD)

Urinary potassium, mean(SD)

Urinary sodium, mean(SD)

Urinary creatinine, mean(SD)

Urine volume, median(IQR)

**Table 2. The effect of intervention on changes of primary outcome and secondary outcomes**

| SS                            |         | SSSC                          |         | p for interaction |
|-------------------------------|---------|-------------------------------|---------|-------------------|
| Difference of outcome (95%CI) | p value | Difference of outcome (95%CI) | p value |                   |
| Primary outcome        |         |                               |         |                   |
| SBP,mmHg                      |         |                               |         |                   |
| Secondary outcome      |         |                               |         |                   |
| DBP,mmHg                      |         |                               |         |                   |
| urinary sodium,mmol/d         |         |                               |         |                   |
| urinary potassium,mmol/d      |         |                               |         |                   |
| microalbumin, mg/d            |         |                               |         |                   |
| serum potassium,mmol/l        |         |                               |         |                   |
| serum sodium,mmol/l           |         |                               |         |                   |

**Table 3. The effect of intervention on adjusted changes of primary outcome and secondary outcomes**

| SS                            |         | SSSC                          |         | p for interaction |
|-------------------------------|---------|-------------------------------|---------|-------------------|
| Difference of outcome (95%CI) | p value | Difference of outcome (95%CI) | p value |                   |
| Primary outcome        |         |                               |         |                   |
| SBP,mmHg                      |         |                               |         |                   |

**Secondary outcome**

DBP,mmHg

urinary sodium,mmol/d

urinary potassium,mmol/d

microalbumin, mg/d

serum potassium,mmol/l

serum sodium,mmol/l

Models were adjusted for

**Table 4. Relative risk for all-cause mortality and cardiovascular events**

| Total N               |      | SS                   |         | SSSC |                      | p for interaction |
|-----------------------|------|----------------------|---------|------|----------------------|-------------------|
| N(%)                  | N(%) | Hazard ratio (95%CI) | p value | N(%) | Hazard ratio (95%CI) |                   |
| All-cause mortality   |      |                      |         |      |                      |                   |
| Cardiovascular events |      |                      |         |      |                      |                   |

**Table 5. Adjusted relative risk for all-cause mortality and cardiovascular events**

| Total N               |      | SS                   |         | SSSC |                      | p for interaction |
|-----------------------|------|----------------------|---------|------|----------------------|-------------------|
| N(%)                  | N(%) | Hazard ratio (95%CI) | p value | N(%) | Hazard ratio (95%CI) |                   |
| All-cause mortality   |      |                      |         |      |                      |                   |
| Cardiovascular events |      |                      |         |      |                      |                   |

Models were adjusted for

**Table 6. Relative risk for safety outcomes**

| Total N                        |      | SS                    |         | SSSC |                       | p for interaction |
|--------------------------------|------|-----------------------|---------|------|-----------------------|-------------------|
| N(%)                           | N(%) | Relative risk (95%CI) | p value | N(%) | Relative risk (95%CI) |                   |
| Incidence of hyperkalemia      |      |                       |         |      |                       |                   |
| Incidence of renal dysfunction |      |                       |         |      |                       |                   |
| Incidence of hyponatremia      |      |                       |         |      |                       |                   |

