## **2.3 Outcome definitions**

The primary outcome for the study is SBP assessed as continuous variable (in mmHg) evaluated during 24-month follow-up.

Secondary outcomes:

- 1) DBP assessed as continuous variable (in mmHg) evaluated during 24-month follow-up.
- 2) 24-hour urinary sodium (in mmol/d), potassium (in mmol/d), and microalbumin excretion (In mg/d) assessed as continuous variable evaluated during 24-month follow-up.
- 3) Incidence of hyperkalemia. A new case of hyperkalemia is defined as having serum potassium  $>5.5$  mmol/L at either month 12 or 24 among participants with normal serum potassium at the baseline, regardless of clinical manifestations.
- 4) the risk of developing all-cause mortality, cardiovascular events (fatal and nonfatal stroke, fatal and nonfatal myocardial infarction, hospitalization or death caused by congestive heart failure)
- 5) ED-5Q during 24-month follow-up.

- 6) Incidence of renal dysfunction: A new case of renal dysfunction is defined as having eGFR <60 at either 12 or 24 months with normal eGFR at the baseline, regardless of clinical manifestations.
- 7) Incidence of hyponatremia: A new case of hyponatremia is defined as having serum sodium <135 mmol/L at either 12 or 24 months with normal serum sodium at the baseline, regardless of clinical manifestations.
- 8) A cost-effectiveness measure will be estimated based on the incremental cost of achieving each 1-mm Hg reduction in SBP

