### **3.1 Confidence intervals and p values**

All applicable statistical tests will be 2-sided and will be performed using a 5% significance level. All confidence intervals presented will be 95% and two-sided.

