### 5.3.2 Randomized comparisons

#### 5.3.2.1 Incidence of hyperkalemia

Only participants without hyperkalemia at baseline will be included in the study. A generalized linear mixed model accounting for clustering will be used for incidence of hyperkalemia

- 1) To evaluate the effect of SS or SSSC alone, the model will be:

The model will include intervention status as fixed effects, as well as cluster as random effects. Thus, the model would be:

$$\begin{aligned} \text{Logit}(P(y_{ij} = 1)) &= \beta_0 + \mu_j + \beta_1 x_{ij} + e_{ij} \\ e_{ij} &\sim N(0, \sigma_e^2) \\ \mu_j &\sim N(0, \sigma_{\mu_j}^2) \end{aligned}$$

Where  $i$  represents the  $i^{\text{th}}$  subjects,  $j$  represents the  $j^{\text{th}}$  cluster (facility),  $y_{ij}$  is the probability of hyperkalemia for subject  $i$  in cluster  $j$ ;  $\beta_0$  is the mean outcome in the control group;  $\mu_j$  is a cluster random effect to allow for between-cluster heterogeneity;  $x_{ij}$ , the predictor of interest, either SS or SSSC, is an indicator of the intervention for subject  $i$  in cluster  $j$  (1 indicates receive intervention while 0 indicates not receive intervention),  $\beta_1$ , the coefficient of interest, is the effect coefficient of intervention;  $e_{ij}$  is the random error for the measurement of subject  $i$  in cluster  $j$ .

2) To test the interaction effect of SS and SSSC, the model will be:

The model will include intervention status as fixed effects, as well as cluster as random effects. Thus, the model would be:

$$\begin{aligned} \text{Logit}(P(y_{ij} = 1)) &= \beta_0 + \mu_j + \beta_1 x_{1ij} + \beta_2 x_{2ij} + \beta_3 x_{1ij} * x_{2ij} + e_{ij} \\ e_{ij} &\sim N(0, \sigma_e^2) \\ \mu_j &\sim N(0, \sigma_{\mu_j}^2) \end{aligned}$$

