### 5.3.2.2 incidence of renal dysfunction

Analysis of incidence of renal dysfunction will follow the same approaches as that for incidence of hyperkalemia.

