**Table 7. Adjusted relative risk for safety outcomes**

| Total N | SS | SSSC |
|---------|----|------|
|---------|----|------|

|                                | N(%) | N(%) | Relative risk
(95%CI) | p value | N(%) | Relative risk
(95%CI) | p value | p for interaction |
|--------------------------------|------|------|--------------------------|---------|------|--------------------------|---------|-------------------|
| Incidence of hyperkalemia      |      |      |                          |         |      |                          |         |                   |
| Incidence of renal dysfunction |      |      |                          |         |      |                          |         |                   |
| Incidence of hyponatremia      |      |      |                          |         |      |                          |         |                   |

Models were adjusted for

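### SAP Tables 6 and 7 label as relative risk what the specified logistic safety model estimates as an odds ratio

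*Supplement*

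**What the plan says.** SAP 5.3.2.1 states: "A generalized linear mixed model accounting for clustering will be used for incidence of hyperkalemia". The equation sets the logit of the event probability equal to an intercept, a facility effect μ_j, β₁ times the intervention indicator, and a normal error e_ij. It names β₁ as the coefficient of interest. The second equation, for the interaction of SS and SSSC, keeps e_ij. The notes say that e_ij "is the random error for the measurement of subject" i in cluster j. The prose introducing each equation lists intervention as the fixed effect and cluster as the random effect, with nothing at subject level.

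SAP 5.3.2.2 extends the model: "Analysis of incidence of renal dysfunction will follow the same approaches as that for incidence of hyperkalemia". SAP 5.3.2.3 repeats that sentence under the hyponatremia heading, evidently meaning hyponatremia.

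SAP 2.3 defines each outcome as one yes/no value per participant. Hyperkalemia is a raised potassium "at either month 12 or 24 among participants with normal serum potassium at the baseline". Renal dysfunction and hyponatremia are built the same way and are likewise counted only in participants who were normal at baseline.

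SAP 6.1 plans "Table 6. Relative risk for safety outcomes" and "Table 7. Adjusted relative risk for safety outcomes". The rows are these three outcomes. The effect columns, not only the titles, say relative risk with a 95% confidence interval, and N(%) columns stand beside them. The remaining safety outcome, mean serum potassium and sodium, uses the linear model (SAP 5.3.2.4) and is not affected.

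**The concern.** Under a logit link exp(β₁) is an odds ratio. With a facility random effect in the model, it is conditional on facility. To obtain a relative risk the analyst would need a log link, a standardisation step or some other conversion, and none is given. Following the text as written, an odds ratio is printed under a relative-risk heading.

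Safety is the first secondary aim in SAP 1.2, which singles out hyperkalemia. A reader of Tables 6 and 7 may multiply the printed ratio by a baseline risk to judge absolute harm. That works for a relative risk. For an odds ratio it overstates the effect, upward or downward, by an amount that grows with the baseline risk.

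The error term raises a smaller question. A participant contributes one binary value, so a further normal error inside the logit has nothing of its own to be estimated from.

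**Working it through.** **No figure to reproduce.** The documents give no event rate, power or effect size for the safety outcomes. The control risks below are assumptions.

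**1. Model against table.** The model is logit P(event) = β₀ + μ_j + β₁x, leaving e_ij aside. For a given facility, changing x from 0 to 1 multiplies the odds by exp(β₁). Nothing in SAP 5.3 or 6.1 turns this into a ratio of risks.

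**2. Size of the gap.** With control risk p₀ and odds ratio OR:

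p₁ = OR·p₀ / (1 − p₀ + OR·p₀), and RR = p₁/p₀ = OR / (1 − p₀ + OR·p₀).

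Example: OR 2.0 and p₀ = 0.10 give p₁ = 0.20/1.10 = 0.1818, so RR = 1.82.

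| Assumed control risk | RR when OR = 1.5 | RR when OR = 2.0 | RR when OR = 3.0 |
|---|---|---|---|
| 1% | 1.49 | 1.98 | 2.94 |
| 2% | 1.49 | 1.96 | 2.88 |
| 5% | 1.46 | 1.90 | 2.73 |
| 10% | 1.43 | 1.82 | 2.50 |
| 20% | 1.36 | 1.67 | 2.14 |
| 30% | 1.30 | 1.54 | 1.88 |

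On the log scale, reading OR 2.0 as a relative risk overstates the effect by ln 2.0 / ln RR − 1. This is about 1.5% at a control risk of 1%, 16% at 10% and 36% at 20%.

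The same happens below 1. OR 0.5 at 20% gives RR = 0.5/(0.8 + 0.1) = 0.56, so the odds ratio makes protection look stronger than it is.

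The conversion uses simple two-group risks. It illustrates the gap and does not reproduce the output of the facility-conditional model.

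**3. Tests.** SAP 3.1 says: "All applicable statistical tests will be 2-sided and will be performed using a 5% significance level". The test of β₁ = 0 is the same whatever the column is called, since OR = 1 exactly when RR = 1 at a given p₀.

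**4. The error term.** Event probabilities within a facility (orders one to three, both arms) were computed from the written model with a facility SD of 0.5 and control risks of roughly 5%, 13% and 28%. They were then refitted with e_ij removed.

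- Error SD 1, β₁ = 0.80: matched without e_ij by β₁ = 0.67 to 0.73, with a largest relative error in any probability of 0.5%.
- Error SD 2, β₁ = 1.07: matched without e_ij by β₁ = 0.66 to 0.78, with a largest relative error of 0.7%.

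The data could not in practice tell these models apart. In strict theory the shape of the link might identify the error SD weakly, but not usefully.

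**The case against.** The best defence is that this is loose vocabulary. Tables 4 and 5 are also titled relative risk, but their columns say hazard ratio, which matches the frailty model in SAP 5.2.2. The phrase therefore looks like an umbrella term. An odds ratio from a mixed logistic model is a legitimate safety measure, and the N(%) columns let a reader see crude risks beside it. All of that stands. It does not remove the mismatch, because in Tables 6 and 7 the column heads themselves say relative risk.

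A reader might infer that the safety results would be materially overstated, above all for renal dysfunction, since SAP 5.6 puts the mean baseline age at about 71. The documents do not support this. SAP 2.3 counts renal dysfunction only in participants with normal eGFR at baseline, so age alone does not make it common, even though the revision table in SAP 5.9 omits that restriction. SAP 5.3.2.1 leaves out participants with hyperkalemia at baseline. No incidence is given for any of the three outcomes, and at 1% to 2% the gap is trivial.

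A reader might also infer that e_ij would inflate the odds ratio. That would require fitting a subject-level effect that the prose does not list. The same error line belongs to the SAP's linear models and appears to have been carried over. A standard random-intercept logistic fit estimates no such term.

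**Conclusion.** The point holds as a labelling and specification gap confined to the three binary safety outcomes. As written, facility-conditional odds ratios would appear in Tables 6 and 7 as relative risks.

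The size depends on control risks that the documents do not give. For an odds ratio of 2.0 the true relative risk would be 1.98 to 1.96 at an assumed 1% to 2%, which is negligible. It would be 1.82 at 10% and 1.67 at 20%, which is material. Whether any of the outcomes is that common cannot be settled from the documents.

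P values and the direction of effect are little affected, so this does not call the safety tests into question. The e_ij term is a notational error for editorial correction.

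**What to change.** Choose one of two routes and state it in SAP 5.3.2.1, so that it carries to 5.3.2.2 and 5.3.2.3:

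- **Relabel.** Change the titles and effect columns of Tables 6 and 7 to odds ratio. This alone cures the mismatch.
- **Keep relative risk.** State that it is obtained by marginal standardisation from the random-facility logistic model, with an interval that respects facility clustering, or from a log-link (modified Poisson) model with facility-clustered standard errors.

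On either route, delete e_ij and its variance line from both logit equations, with the matching phrase in the notes, and correct the outcome named in 5.3.2.3.

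Relabelling costs SAP wording only. Estimating relative risks adds a small amount of code per outcome. Neither route needs new data or a design change.

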There have already been many large-scale randomized controlled trials showed that salt substitutes can lower the blood pressure of people with hypertension. However, the long-term efficacy of salt substitutes on lowering the blood pressure of the average elderly population remains unclear. Furthermore, the main components of salt substitutes include sodium chloride and potassium chloride. Compared to regular salt, consuming the salt substitute that contains less sodium and more potassium can increase the intake of potassium, which might potentially affect the urine potassium, blood potassium and kidney function. Even though the Food and Drug Administration has deemed salt substitutes containing potassium chloride as safe in 1983 and reported that no adverse reactions were observed in the consumption of salt substitutes amongst the people with normal kidney function, the safety of these intervention strategies on the elderly population still lack ample evidence. Further research is required to obtain the relevant data, so as to build a solid foundation for the large-scale promotion of salt reduction strategies in the future.

Currently, salt substitutes on the market contain no more than 30% less sodium chloride than regular salt. Judging from the average salt consumption level of our population, merely using salt substitutes cannot push the Chinese diet toward the recommended salt intake in Chinese Dietary Guidelines. The centralized provision of meals for the elderly in nursing homes makes the kitchen of these nursing homes an optimal trial site for the salt reduction strategies. A research project targeted at reducing the salt intake of the collective elderly population in the US adopted a gradual

and acceptable approach to salt reduction. The intervention strategies used were targeted at the supply of meals for the elderly and the kitchen of the nursing homes. Specifically, the intervention strategies like replacing high-sodium foods with low-sodium foods, improving recipes, and changing the ways cooks prepared the foods were adopted. Ultimately, the sodium content of the meals supplied to the elderly decreased by 9.76% in the first year and 14.17% in the second year.

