#### **➤ Management Target and Plan for Gradual Reduction of Cooking Salt Usage**

The main strategy behind this intervention is to control the person purchasing salt for the nursing homes, so as to gradually reduce salt usage in the kitchen in a stepwise manner. The intervention strategy consists of 4 stages. The first stage is the preparatory stage, which lasts for a month. The nursing homes will continue the amount of salt they normally use in their cooking and begin recording how much salt they use to be used as a baseline reference. The second stage consists of two steps, with every step lasting 3 months for a total of 6 months. At this stage, the salt reduction target for every step will be 10% from the nursing home's baseline salt usage. The third stage consists of four steps, with every step lasting 3 months for a total of 12 months. At this

stage, the salt reduction target for every step will be 5% from the nursing home's baseline salt usage. The fourth stage is the maintenance stage. The amount of salt used in the nursing homes should now decrease to 60% of their baseline salt usage. This will not be lowered further until the end of the research. (As per diagram below)

[figure not shown]

➤ Management of Stepwise Salt Supply Control and evaluation

Nursing homes that have been assigned to the SSSC group will send their purchasers and cooks to receive standardized technical training. See Annex 2 (Stepwise Salt Supply Control Technical Training) for detailed contents of the training.

Through the training, purchasers will learn and understand the salt reduction targets throughout the various stages and the specific ways to control salt supply; and cooks will learn how to weigh 5% and 10% of their ordinary salt usage. The two parties have to learn the reason for salt reduction and techniques to communicate with the elderly.

The person-in-charge from the sub-sites will audit the stock in and stock out records once every three months to evaluate if the goal for the stage has been met. This will be the basis for the

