### **1.2 Objectives**

The primary aim of the present study is to determine the efficacy of two practical and scalable sodium reduction intervention strategies on systolic blood pressure (SBP) among older adults living in senior residential facilities: (1) a stepwise reduction in the supply of regular salt to institutional kitchens and (2) replacing regular salt with salt substitute. The null hypothesis is that neither of the two sodium reduction interventions will reduce SBP. And if the effect of both interventions do exist, the interaction between SS and SSSC in lowering SBP during study period will be further analyzed.

The secondary aims are to:

- 1) evaluate the safety of these strategies, particularly risks of hyperkalemia with salt substitute and hyponatremia in those receiving either or both interventions.
- 2) evaluate whether sodium reduction intervention can reduce the risk of cardiovascular events and death
- 3) assess the cost-effectiveness and adherence of sodium reduction strategies
- 4) assess the impact of sodium reduction intervention on microalbuminuria

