## **2. Study design**

### **2.1 Trial design**

DECIDE-Salt is a 2-year  $2 \times 2$  factorial, cluster randomized controlled trial testing the efficacy, safety, and cost-effectiveness of 2 intervention strategies for reducing dietary sodium intake

among older adults in residential facilities. The 2 interventions are (1) a controlled stepwise reduction of salt supply (SSSC) compared to “usual care (no reduction in salt supply)” and (2) introduction of low sodium salt substitute (SS) compared to regular salt. Each facility is randomly assigned to 1 of 4 groups: both SSSC and SS, SSSC only, SS only, and neither.

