## **2.4 Randomization**

The 48 eligible senior residential facilities (clusters) were randomized through a central computerized process in a 1:1:1:1 allocation ratio to the 4 intervention groups, with stratification by four regions, (Changzhi , Xi'an, Hohhot and Yangcheng). An independent statistician carried out the randomization after the baseline characteristics had been collected for study sites and individual participants. The allocation codes are kept by the statistician, and only the local staff responsible for the implementation of interventions have been informed. The outcome assessment team is independent of the staff responsible for implementing the interventions

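### SAP Tables 6 and 7 do not report the combined SS+SSSC arm, although the safety aim covers hyponatremia in residents on both interventions

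*Supplement*

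**What the plan says.** The SAP's first secondary aim (1.2) is safety, "particularly risks of hyperkalemia with salt substitute and hyponatremia in those receiving either or both interventions". The design has four arms (SAP 2.1): "Each facility is randomly assigned to 1 of 4 groups: both SSSC and SS, SSSC only, SS only, and neither". The 48 facilities "were randomized through a central computerized process in a 1:1:1:1 allocation ratio to the 4 intervention groups" (SAP 2.4).

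SAP 5.3.2.1 gives two logistic mixed models for hyperkalemia. The first has one indicator, SS or SSSC, coded 1 for residents who receive it and 0 for those who do not, so it estimates a factorial margin. The second has SS, SSSC and their product, and is introduced with "To test the interaction effect of SS and SSSC, the model will be". It is planned without any condition. Section 5.3.2.3 carries the same approach over to hyponatremia; its sentence names renal dysfunction, evidently a slip.

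Results go to "Table 6. Relative risk for safety outcomes" and "Table 7. Adjusted relative risk for safety outcomes". Each has a total, an SS block (N(%), relative risk, p), an SSSC block and a p for interaction. There is no SS+SSSC column and no control column.

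For SBP, SAP 5.1.1 commits to reporting the two main coefficients and the interaction coefficient with 95% CIs. No such commitment is made for safety outcomes. Protocol V1.4, section 9 (Safety Evaluation) plans to compare SS+SSSC with SS only or SSSC only on potassium, hyperkalemia and other adverse reactions. The SAP's list of revisions (5.9) does not withdraw that plan.

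**The concern.** The aim names residents on both interventions, but nothing in the hyponatremia rows describes them separately. The SS and SSSC columns each pool the combined arm with one single-intervention arm. Each relative risk then compares that pool with a group in which half the facilities receive the other intervention.

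The combined arm has the largest planned sodium cut. For SSSC the protocol's end target is: "The amount of salt used in the nursing homes should now decrease to 60% of their baseline salt usage". Its Background says that "salt substitutes on the market contain no more than 30% less sodium chloride than regular salt". Taken together, kitchen-salt sodium could fall to 0.60 × 0.70 = 0.42 of baseline, a cut of up to 58%, against 40% for SSSC only and up to 30% for SS only. If the combination carried a hyponatremia risk beyond what the single interventions suggest, the published tables would give neither its size nor its precision.

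**Working it through.** **1. The plan's own figures.** 48 facilities × 20 = 960 residents. Per arm: 48/4 = 12 facilities and 960/4 = 240 residents. Per margin: 960/2 = 480. These match the 2 × 2 table in protocol V1.4, section 10.

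**2. Can the combined-arm count be recovered?** Let a, b, c, d be the cases in control, SS only, SSSC only and both. The tables give T = a+b+c+d, S = b+d and C = c+d: three sums for four unknowns. For example, (a, b, c, d) = (12, 12, 12, 33) and (2, 22, 22, 23) both give T = 69, S = 45, C = 45. Only the difference d − a = S + C − T = 21 is fixed. The level and the ratio are not: 33/12 = 2.75 against 23/2 = 11.5.

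**3. Does the planned model contain the estimate?** Yes. In the two-factor model the log odds ratios against control are b1 (SS only), b2 (SSSC only) and b1+b2+b3 (both). A saturated logistic fit to rates built with an odds ratio of 3 for both returns 3.00.

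**4. With interaction.** The documents give no hyponatremia rate, so the rates here are assumptions: 5% in control and both single arms, odds ratio 3 with both.
- Odds with both: 3 × 0.05/0.95 = 0.1579, so the risk is 0.1579/1.1579 = 0.1364.
- Both against neither: RR = 0.1364/0.05 = 2.73.
- Each margin: (0.05 + 0.1364)/(0.05 + 0.05) = 1.86.
- Multiplying the margins does not repair this: 1.864 × 1.864 = 3.47, which overshoots 2.73.

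**5. Power in that case** (Wald approximation, two-sided 5%; 12 facilities per arm; 16 evaluable each after 20% loss; ICC 0.02 borrowed from the SBP design).
- Effective n per arm = 12 × 16/(1 + 15 × 0.02) = 192/1.3 = 147.7.
- Variance of a log odds = 1/(n p(1−p)): 0.1425 at 5%, 0.0575 at 13.64%.
- Interaction: SE = √(3 × 0.1425 + 0.0575) = 0.697; z = ln 3/0.697 = 1.58; power about 35%.
- Both against neither: SE = √(0.1425 + 0.0575) = 0.447; z = 2.46; power about 69%.

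Same pattern at other assumed control rates:

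| Control rate | RR, both v neither | RR, each margin | Power, interaction | Power, both v neither |
|---|---|---|---|---|
| 2% | 2.88 | 1.94 | 17% | 36% |
| 5% | 2.73 | 1.86 | 35% | 69% |
| 10% | 2.50 | 1.75 | 57% | 91% |

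**6. Without interaction.** Control 5%, odds ratio 1.5 for each intervention, so 1.5 × 1.5 = 2.25 for both. The product of the two odds ratios is the combined odds ratio. On the relative-risk scale each margin shows 1.45 and both against neither is 2.12; 1.45 × 1.45 = 2.10, close to it.

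**7. Scale.** The models are logistic, so they give odds ratios, while both tables are headed relative risk. In step 4 the same effect is 3.00 as an odds ratio and 2.73 as a relative risk.

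**The case against.** The strongest reply is that nothing is missing from the analysis. The interaction model is unconditional, applies to hyponatremia by cross-reference, and yields the combined-arm effect as a linear combination. This stands. A reader might infer from the shells that the combined arm has no planned estimate; SAP 5.3.2.1 does not support that.

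Second, margins are the ordinary summary of a factorial trial. A reader might infer that the combined arm's risk is simply averaged away. The documents do not support that either: without interaction on the logit scale the product of the margins gives the combined odds ratio (step 6), and the excess case count over control follows from the columns (step 2). The loss is real only with interaction, and there the p for interaction is a safeguard of low power that gives no effect size or interval.

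Third, the protocol already plans safety contrasts of SS+SSSC with each single intervention. True, but they are not against control, do not name hyponatremia and have no place in the SAP tables.

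Fourth, the aim may only name who is at risk, and residents on both are included in both margins; the shells are also headed as main tables and need not be exhaustive. That is a fair reading, but no other section promises the result.

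Fifth, the 58% is a ceiling. It is an end target for kitchen salt only, and the 30% is a market figure, not the study product's composition. On the step schedule the SSSC target at month 12, also a hyponatremia time point, is a 30% cut, giving 1 − 0.70 × 0.70 = 51% with both. The documents give no relation between sodium cut and hyponatremia, so these figures only rank the arms.

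**Conclusion.** The point holds as a reporting gap. The safety aim covers hyponatremia with both interventions, while Tables 6 and 7 show the two margins and an interaction p value. The combined arm's count, effect size and interval are not reported, and no text commits to reporting them, as 5.1.1 does for the SBP coefficients.

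The size depends on whether the interventions interact. In the central illustration a relative risk of 2.73 sits behind two margins of 1.86, with about 35% power to flag the interaction against about 69% for the direct contrast. Those figures rest on assumed event rates, an ICC borrowed from SBP and a normal approximation. Without interaction the combined odds ratio can be rebuilt from the margins, though not with a confidence interval. No data, randomisation or primary conclusion is affected.

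**What to change.** In Tables 6 and 7, add N(%) for all four arms, grouped as the safety set already defines (intervention received). For hyponatremia, add SS only, SSSC only and SS+SSSC, each against control with 95% CI, from b1, b2 and b1+b2+b3 of the planned two-factor model (its adjusted form for Table 7). Keep the marginal columns and the p for interaction. State this commitment in 5.3.2, correct the outcome named in 5.3.2.3, and say in 5.9 whether the protocol's SS+SSSC safety contrasts are kept. Label the estimates as odds ratios, or convert them and say how.

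No new data or model is needed. The price is precision: each contrast rests on 12 against 12 facilities. In the 5% illustration the 95% CI runs a factor of 2.40 either way, about 1.25 to 7.2 around an odds ratio of 3. At a 2% rate only about 192 × 0.02 = 4 control cases would be expected, so the model estimates may be unstable and the arm counts would carry most of the information.
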